### Randomisation

Once recruited and ethical clearance gained, the lead CI will perform simple randomisation of the maternity sites to either the intervention or control arm via a computerised method. Those in the intervention arm will receive monthly GCS in their maternity units, and those in the control arm will not. The study design and nature of the intervention means that blinding for staff will not be possible.

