**Methods:**

This study will be a cluster randomised controlled trial of maternity sites within Sydney and the surrounding districts. Twelve sites will be recruited and half will receive monthly Clinical Supervision for up to two years. Midwives from all sites will be requested to complete 6-monthly surveys comprising validated measurement tools: the Copenhagen Burnout Inventory (CBI), the Australian Midwifery Workplace Culture (AMWoC) tool and the Clinical Supervision Evaluation Questionnaire (CSEQ) (the latter for intervention sites only). Primary outcomes are the levels of burnout in midwives (using the CBI). Secondary outcomes will be the quality of the intervention (using the CSEQ), perceptions of workplace culture (using the AMWoC tool) and midwives’ intention to stay in their role/profession, as well as sick leave rates and numbers of exiting staff. We will also determine the dose effect – ie the impact in relation to how many Clinical Supervision sessions the midwives have attended, as well as other supportive workplace strategies such as mentoring/coaching on outcomes.

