### Sample size

Assuming that 67% of midwives will have moderate or high levels of burnout [18], a sample size of 744 (373 per arm) from twelve maternity sites with an average of 62 midwives per site will achieve 80% power to detect a 15% decrease in moderate or greater burnout with an α level of 0.05 and intra-class correlations of 0.02. Assuming 20% attrition, the target sample size is 894 (447 midwives). This equates to an average of 75 midwives per site.

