### Statistical analysis

Data will be analysed using SPSS on an intention-to-treat approach. Initially descriptive statistics will be used to compare the two groups at baseline, recognising that clustered randomisation does not necessarily achieve balance on covariates at the individual level. The primary outcome, the Copenhagen Burnout Inventory (CBI) will be assessed to calculate the percentage of midwives with moderate or higher levels of burnout. This percent will be ascertained for all midwives in both trial arms every six months. The main analysis will be logistic regression using generalised estimating equations (GEE) to test the main hypothesis related to reduction in burnout rate. Secondary analyses will estimate the impact of the programme on the other relevant outcomes. All analyses will be adjusted for the effect of clustering using generalised estimating equations and will also be adjusted for the variable used in stratification. Counts will be analysed with Poisson regression, binary outcomes with logistic regression and continuous scales with linear regression. Although confounding is not expected to be an issue due to the randomisation, any key variables showing large imbalances by randomisation group will be added to the model. Multiple imputation will be performed on missing data to minimise any potential bias. An intention to treat approach will be used.

The qualitative data within the AMWoC survey will be analysed thematically using the six step approach by Braun and Clarke [44].

Triangulation of quantitative and qualitative data, and the workforce data on turnover and sick leave will provide further insights into the relationship between GCS, midwifery workplace culture and staff turnover. Analyses will occur following each data collection period and amalgamated at the end of the study. The biostatistician responsible for data analysis will be blinded to the maternity site data (within the REDCap database). It is not possible to blind the allocation of the intervention to the maternity site staff and other researchers/Principal Investigators. Figure 1 shows the study progression timeline.

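### The Randomisation section describes simple randomisation of sites, but every analysis is to adjust for an unnamed stratification variable; read literally, the method also does not secure the planned 6:6 split

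*Protocol article*

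**What the plan says.** - Protocol article, Randomisation: "the lead CI will perform simple randomisation of the maternity sites to either the intervention or control arm via a computerised method". The section mentions no stratification factor, blocking or fixed number of sites per arm.
- Protocol article, Statistical analysis: clustering is handled by GEE, and all analyses "will also be adjusted for the variable used in stratification". The wording presupposes one particular variable. No section names it or describes stratified allocation.
- Protocol article, Abstract (Methods): "Twelve sites will be recruited and half will receive monthly Clinical Supervision for up to two years".
- Protocol article, Sample size: "a sample size of 744 (373 per arm) from twelve maternity sites with an average of 62 midwives per site". The control rate is given by "Assuming that 67% of midwives will have moderate or high levels of burnout", and the design "will achieve 80% power to detect a 15% decrease in moderate or greater burnout with an α level of 0.05 and intra-class correlations of 0.02". The calculation is for two equal arms.

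**The concern.** The main problem is a contradiction between two positive statements. It is not a detail left for a fuller document: an analysis plan could name a stratification variable, but the Randomisation section would still describe a method that has none. The adjustment applies to all analyses, including the primary logistic GEE model. As written, a reader cannot tell how sites are allocated or what the primary model adjusts for. With 12 clusters, a site-level covariate chosen late could move both the estimate and its standard error, and the article plans analyses after each six-monthly collection.

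The second problem depends on what simple means. The abstract promises the intervention to half the sites, and the sample size rests on equal arms. Independent draws do not guarantee either. An uneven split of a small, fixed number of sites costs power that could be kept at almost no expense.

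**Working it through.** **Inputs (Sample size section).** Control rate 67%; decrease 15%, taken as percentage points (67% to 52%) because that is the reading that reproduces the stated size; α 0.05, taken as two-sided for the same reason; power 80%; ICC 0.02; 12 sites; 62 midwives per site.

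**Step 1: reproduce the stated sample size.**

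- Individually randomised, pooled variance, no continuity correction: n = [1.96·√(2·0.595·0.405) + 0.8416·√(0.67·0.33 + 0.52·0.48)]² / 0.15² = 166.9, so 167 per arm.
- Design effect: 1 + (62 − 1)·0.02 = 2.22.
- 167 × 2.22 = 370.7, so 371 per arm against the stated 373. This is within rounding.
- Variants that do not reproduce it: one-sided test 293 per arm, continuity correction 402, 15% relative decrease 813.

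The stated 80% therefore rests on two equal arms, that is, six sites each at 62 per site.

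**Step 2: power formula for any split.** With k₁ control and k₂ intervention sites, the effective sizes are n₁ = 62k₁/2.22 and n₂ = 62k₂/2.22.

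- SE = √(0.67·0.33/n₁ + 0.52·0.48/n₂).
- Unpooled: power = Φ(0.15/SE − 1.96).
- Pooled: power = Φ((0.15 − 1.96·SE₀)/SE), where SE₀ is the standard error under the pooled rate.

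At 6:6, n₁ = n₂ = 372/2.22 = 167.6 and SE = 0.0530. Unpooled: 0.15/0.0530 − 1.96 = 0.870, power 80.8%. Pooled: SE₀ = 0.0536, power 80.1%.

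With 4 control and 8 intervention sites, n₁ = 111.7, n₂ = 223.4 and SE = 0.0556. Unpooled power is 76.9%, pooled 75.0%.

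**Step 3: probability of each split under independent 1:1 draws.** P(k sites in one arm) = C(12, k)/4096, counting both directions for uneven splits. Power ranges cover either arm being the larger.

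| Split | Ways of 4096 | Probability | Power, pooled | Power, unpooled |
|---|---|---|---|---|
| 6:6 | 924 | 22.6% | 80.1% | 80.8% |
| 5:7 | 1584 | 38.7% | 78.9-79.2% | 79.3-80.1% |
| 4:8 | 990 | 24.2% | 75.0-75.8% | 75.2-76.9% |
| 3:9 | 440 | 10.7% | 67.4-69.0% | 67.5-70.2% |
| 2:10 | 132 | 3.2% | 54.0-56.9% | 54.3-57.7% |
| 1:11 or 0:12 | 26 | 0.6% | not tabulated | not tabulated |

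- 4:8 or more uneven: (990 + 440 + 132 + 26)/4096 = 1588/4096 = 38.8%.
- 3:9 or more uneven: 598/4096 = 14.6%.
- Average power over all splits: 76.2% pooled, 76.8% unpooled, about 4 points below 6:6.

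**Step 4: the alternative reading.** If six of the 12 sites are drawn at random in one step, P(6:6) = 1 and the stated 80% stands. No stratification variable arises under this reading either, so the conflict with the Statistical analysis section is unchanged.

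**The case against.** The strongest reply is that this is loose wording. Sites are randomised after recruitment, the abstract says half get the intervention, and one computerised draw of six from 12 fits both. On that reading the unequal-split figures fall away. This stands, and it is why the 22.6% and the power losses are conditional. Even under independent draws, about 61% of allocations (5:7, 6:6 or 7:5; 2508/4096) lose at most about 1.5 points of power.

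Several stronger inferences are tempting, but the documents do not support them:

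- *That the stratification variable does not exist.* The text shows only that it is unnamed and that the allocation paragraph describes no stratification. Stratified allocation may have been intended and left out.
- *That the primary model cannot be fitted.* If there was no stratification, the clause can be deleted and the logistic GEE model fitted. The defect is an undefined covariate.
- *That uneven splits inflate the type I error by a known amount.* Any figure would need an assumed spread of site sizes and an uncorrected GEE variance. The article gives neither. How well a normal approximation serves 12 clusters is a separate question, independent of how sites are allocated.
- *That large or high-burnout units will probably fall in one arm.* The documents give no between-site data beyond the ICC of 0.02, and the Statistical analysis section provides for adding key variables that show large imbalance. That does not prevent imbalance, but it is a stated mitigation.

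None of this removes the contradiction between the two sections.

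**Conclusion.** The concern holds in two parts of different strength.

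1. **Unconditional.** The Randomisation and Statistical analysis sections conflict. One describes allocation without strata; the other adjusts every analysis for a stratification variable that is never identified. A covariate in the primary model is therefore undefined. This holds on either reading of simple.
2. **Conditional on independent 1:1 draws per site.** The half-and-half allocation is more likely missed than met (22.6% for 6:6). The cost is about 1 point of power at 5:7, about 4 to 6 at 4:8 and about 11 to 13 at 3:9, or about 4 points on average. These figures assume 62 analysed midwives at every site, ICC 0.02, a 67% to 52% difference, two-sided α 0.05 and a normal approximation, which are the inputs that reproduce the stated sample size.

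The power loss is modest on average but avoidable. The contradiction must be resolved whatever the split.

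**What to change.** **If sites are not yet allocated.** Replace simple randomisation with restricted allocation fixed at six sites per arm, then choose one of two consistent versions:

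- Stratify or constrain on one site-level factor known beforehand, for example the number of eligible midwives. Name it in the Randomisation section and again as the adjustment variable in the Statistical analysis section.
- Leave the 6:6 draw unstratified and delete the stratification adjustment.

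**If sites have already been allocated.** Describe the method actually used, including whether 6:6 was fixed. Name the stratification variable if there was one, or delete the adjustment if not. If the realised split is not 6:6, restate power for that split.

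**Cost.** A paragraph of text and, before allocation, a short program. Fixing 6:6 costs no sites or midwives and keeps the stated 80%. Adjusting for one two-level site factor uses about one of some 10 cluster degrees of freedom (12 sites less two arms).

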### Data collection and management

Six-monthly online survey data collection will occur for all sites using the AMWoC instrument, the CSEQ (for intervention sites), and the CBI; all validated tools (see Outcome Measures above). Hardcopy surveys will be available for participants. Similarly, non-identifiable numerical workforce data on midwifery staff turnover and sick leave will be collected. We will also determine the dose effect – i.e. we will measure how many GCS sessions the midwives have attended (whether study-related or sessions already offered at their workplace), as well as other supportive workplace strategies such as mentoring/coaching.

Data management plans have been lodged within the [*blinded*] Data Management Plan portal. This describes that data is contained within the cloud-based, daily backed-up REDCap platform. Any hardcopy data (hardcopy versions of the online survey) will be transcribed into this platform by the Research Assistant. Similarly, completed consent forms will be scanned and uploaded to REDCap. All data will be transferred and stored for 15 years within the Data Management Plan portal once the project is completed.

Confidentiality will be maintained throughout the management of the survey data. Data will be non-identifiable, coded and de-personalised. All study-related information will be stored securely at the Sponsor site. All participant information will be stored in locked file cabinets in areas with limited access, before being scanned and stored on a cloud-based secure, password protected computer. All administrative forms will be identified by a coded ID number only to maintain participant confidentiality. All records that contain names or other personal identifiers, such as locator forms and informed consent forms, will be stored separately from study records identified by code number. Limited personnel will have access to data (the Chief Investigator, Research assistant and Biostatistician). Project Principal Investigators will have no access to their own site’s data sets.

### Statistical analysis

Data will be analysed using SPSS on an intention-to-treat approach. Initially descriptive statistics will be used to compare the two groups at baseline, recognising that clustered randomisation does not necessarily achieve balance on covariates at the individual level. The primary outcome, the Copenhagen Burnout Inventory (CBI) will be assessed to calculate the percentage of midwives with moderate or higher levels of burnout. This percent will be ascertained for all midwives in both trial arms every six months. The main analysis will be logistic regression using generalised estimating equations (GEE) to test the main hypothesis related to reduction in burnout rate. Secondary analyses will estimate the impact of the programme on the other relevant outcomes. All analyses will be adjusted for the effect of clustering using generalised estimating equations and will also be adjusted for the variable used in stratification. Counts will be analysed with Poisson regression, binary outcomes with logistic regression and continuous scales with linear regression. Although confounding is not expected to be an issue due to the randomisation, any key variables showing large imbalances by randomisation group will be added to the model. Multiple imputation will be performed on missing data to minimise any potential bias. An intention to treat approach will be used.

The qualitative data within the AMWoC survey will be analysed thematically using the six step approach by Braun and Clarke [44].

Triangulation of quantitative and qualitative data, and the workforce data on turnover and sick leave will provide further insights into the relationship between GCS, midwifery workplace culture and staff turnover. Analyses will occur following each data collection period and amalgamated at the end of the study. The biostatistician responsible for data analysis will be blinded to the maternity site data (within the REDCap database). It is not possible to blind the allocation of the intervention to the maternity site staff and other researchers/Principal Investigators. Figure 1 shows the study progression timeline.

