## Methods/design

The multicentre parallel cluster randomised controlled trial (RCT) will comprise 12 maternity sites with a primary objective of determining burnout levels of midwives in relation to the provision of Group Clinical Supervision (GCS), the intervention. Secondary objectives will be measuring perceptions of workplace culture and the efficacy of the GCS intervention itself in relation to GCS. Staff attrition and sick leave rates of midwives will also be measured during the study period.

It is hypothesised that regular GCS will improve midwives’ perceptions of their workplace culture and lower their levels of work-related burnout (primary outcome); that midwives with positive perceptions of their workplace culture will be more likely to remain in their profession; and maternity units that support midwives to attend regular GCS will have lower levels of midwifery staff attrition and sick leave than those that do not (secondary outcome).

Quantitative and qualitative data will be collected in this study. Validated quantitative tools will be used: the Australian Midwifery Workplace Culture (AMWoC) instrument [37], the Copenhagen Burnout Inventory (CBI) [38] and the Clinical Supervision Evaluation Questionnaire (CSEQ) [39] (intervention sites only). These are described more fully below. The survey platform REDCap ([Research Electronic Data Capture] a secure web application for building and managing online surveys and databases) will be used.

Participants in the intervention sites will be requested to attend GCS sessions as much as is practicable, but at least twice in a six-month period. Surveys will be emailed to participants every six months that contain the tools listed above, and simple demographic/workplace questions. Participant surveys in control sites will not contain the CSEQ. The number of GCS sessions or other supportive strategies (such as mentoring/coaching) that all participants have undertaken will be measured. The CONSORT statement for cluster RCTs will be used to ensure rigour and process [40].

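### The primary GEE test rests on 12 sites with no small-sample correction stated; run in the usual uncorrected way, its nominal 5% level is about 10%, and correcting it lowers the stated 80% power to about 72%

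*Protocol article*

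**What the plan says.** The Methods/design section fixes the number of clusters: "The multicentre parallel cluster randomised controlled trial (RCT) will comprise 12 maternity sites". The abstract gives the intended split: "Twelve sites will be recruited and half will receive monthly Clinical Supervision for up to two years". The Randomisation section says that "the lead CI will perform simple randomisation of the maternity sites to either the intervention or control arm via a computerised method", a method that does not by itself guarantee six sites per arm.

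The Statistical analysis section sets the primary test: "The main analysis will be logistic regression using generalised estimating equations (GEE) to test the main hypothesis related to reduction in burnout rate". It applies the same approach throughout: "All analyses will be adjusted for the effect of clustering using generalised estimating equations". It also says that models will be adjusted for a stratification variable and for any key variable with a large imbalance. It names the software: "Data will be analysed using SPSS on an intention-to-treat approach".

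No section mentions a bias-corrected variance, a t or F reference distribution, a permutation test or a site-level analysis. None says that the variance will be uncorrected either.

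**The concern.** The robust variance in GEE and its normal-reference Wald test are justified when the number of independent clusters is large. Here that number is 12, and recruiting more midwives per site does not raise it. With few clusters, two errors point the same way: the sandwich variance is too small on average, and the normal distribution ignores the uncertainty in that variance. Site-level covariates reduce the roughly 10 available degrees of freedom further.

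At stake is the error rate of the headline test on burnout and of every secondary model that follows the same rule. A programme with no effect could be declared beneficial more often than the stated 0.05 implies, with intervals that look more precise than they are.

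**Working it through.** **Inputs.** From the Sample size section: burnout prevalence 67%, a 15% decrease, α 0.05, power 80%, ICC 0.02, 744 midwives in all, 62 per site, 12 sites. Assumed, because the article gives only an average site size: the CV of site size.

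**1. Reproduce the plan's own figure.** Reading the decrease as absolute (67% to 52%), a two-sided comparison of two proportions with normal critical values needs 167 per arm. The design effect is 1 + 61 × 0.02 = 2.22. Then 167 × 2.22 = 370.7 per arm, or 741 in total, close to the stated 744. A relative 15% decrease would need about 1,625, and a continuity correction about 804. So 744 matches normal critical values with no allowance for degrees of freedom.

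**2. Analytic type I error, six equal sites per arm.** The uncorrected sandwich standard error is too small by √(5/6) = 0.913. The actual rejection rate is P(|t10| > 1.96 × 0.913) = P(|t10| > 1.789) = 10.4%.

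**3. Interval width.** Relative to a valid t(10) interval: (1.96 / 2.228) × 0.913 = 0.803, so about 20% too narrow. Simulated coverage is about 90%, and about 88% at a size CV of 0.5.

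**4. Simulation under the null.** Beta-binomial data, 67% prevalence, ICC 0.02, average 62 per site, 40,000 runs per scenario. The last column uses a Kauermann-Carroll variance with t(10).

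| Sites per arm | Size CV | Uncorrected, normal | Corrected, t(10) |
|---|---|---|---|
| 6:6 | 0 | 10.1% | 4.8% |
| 6:6 | 0.3 | 11.1% | 5.2% |
| 6:6 | 0.5 | 12.2% | 5.7% |
| 6:6 | 0.7 | 14.2% | 6.6% |
| 5:7 | 0 | 10.9% | 5.3% |
| 4:8 | 0 | 12.2% | 6.1% |
| 3:9 | 0 | 15.8% | 8.3% |

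A separate simulation of 20,000 runs gave 12.9% for 4:8, hence the range 12-13%. With equal sites, the uncorrected rate stays near 10% for ICCs from 0.001 to 0.05, so it does not depend on the assumed ICC. The more conservative Mancl-DeRouen variance with t(10) gives 3.2-3.5% with equal sites.

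**5. Full GEE fits** (exchangeable working correlation, 1,500 runs each). The uncorrected robust test rejects 10.5% with equal sites, 12.3% at CV 0.5, and 11.4% with equal sites and one site-level covariate. The model-based standard error does no better: 10.5%, 12.6% and 11.2%.

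**6. Chance of an uneven split.** If simple randomisation means an independent fair allocation for each site, a 4:8 or more extreme split has probability 2 × 794/4096 = 39%.

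**7. Power after correction.** The standard error of the difference is √[(0.67 × 0.33 + 0.52 × 0.48) / (372/2.22)] = 0.0530, and 0.15/0.0530 = 2.83. With normal critical values, power is Φ(2.83 - 1.96) = 81%. With t(10), from the noncentral t distribution, it is 72%. Seven sites of 62 per arm would give about 80%.

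**The case against.** The strongest reply is that the flaw is inferred from silence. The article names the model but no variance estimator, test statistic or reference distribution, and those details are commonly left to a statistical analysis plan, which is not shown here. A GEE with a corrected variance and a t reference would satisfy the text as written. The simulations are also simpler than the planned analysis: they model one survey, without repeated measures or multiple imputation.

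Much of this stands, and it limits the claim. A reader might infer that the trial's false-positive rate is double the stated level. The article does not support that, because it leaves the correction open. A reader might also take 12% as the expected rate. That needs a site-size CV near 0.5, which the article does not give, or a 4:8 split, which simple randomisation permits but which departs from the stated half and half. Nor does the article show that SPSS cannot produce the correction; that has to be checked.

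The objection does not remove the point. The article commits the primary test, and all handling of clustering, to a method whose ordinary use is invalid with 12 clusters. Its sample size matches normal critical values. A later plan can restore the 5% level, but the published 80% power would then no longer hold. Modelling repeated surveys would not help either, since the number of independent sites stays at 12.

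**Conclusion.** The concern holds in conditional form. If the primary GEE is run as the usual uncorrected Wald test with a normal reference, its type I error is about 10% with equal sites split 6:6, and its intervals are about 0.80 times the valid width. This base case needs no assumption about the ICC. The rate is about 11-12% under an assumed size CV of 0.3-0.5 and about 12-13% under a 4:8 split.

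The defect is an inference method left open where the default is wrong, together with a power figure that makes no allowance for the correction. It is not proof that the trial will be analysed at the wrong level. The power figure of about 72% rests on the article's own inputs with equal sites and no site-level covariates.

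**What to change.** Keep the GEE logistic model with site as the cluster, which also covers repeated surveys from the same midwife. For the primary and secondary models, specify:

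- a bias-corrected sandwich variance, for example Kauermann-Carroll or Fay-Graubard;
- a t reference on 12 - 2 - (number of site-level covariates) degrees of freedom;
- a site-level t-test or permutation test as confirmation.

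Check whether the SPSS procedure can produce the corrected variance. If it cannot, run these models in software that can. Restate the power for 67% versus 52% at an ICC of 0.02 as about 72% with 12 sites.

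The cost is a few sentences in the analysis section and possibly a second package. Intervals widen and power falls by about 8 to 9 points. The correction is also not exact under strong imbalance: in the simulations it gave 6.1% at 4:8 and 8.3% at 3:9, which is a further reason for the confirmatory test.
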